### Description of the intervention

The “StepUp” intervention is a 6-week pedometer-based physical activity program for children with physical disabilities. It comprises two face to face visits and fortnightly phone follow ups with the physiotherapist, provision of a pedometer and StepUp handbook. There are two versions of the handbook - one for 8–12 year olds, and one for 13–17 year olds. The core content of the handbooks is the same, however the amount and complexity of the written content vary between the two age groups to accommodate the wide range of reading skills and age-appropriate content between the groups. Graphic design of the handbook has been undertaken by [name], who has expertise in the design and presentation of written information for children with reading difficulties, supplemented by illustrations from a professional illustrator. Further details of the intervention components and materials are provided in Table 1 and Figure 1. Week 1 of the StepUp program is being used to determine baseline activity levels (note this is distinct from the baseline outcome measurement period, which used an accelerometer to measure physical activity, and takes place prior to the participant being assigned to either the intervention or control group). Progressive daily targets are then negotiated by telephone between the physiotherapist and participant on a fortnightly basis.

**Table 1 T1:** Description of the StepUp program

**Components**	**Description**
Contact with therapist	Week 1– face to face visit to introduce StepUp program
	Week 2 and week 4 – 5 minute phone call to negotiate weekly step count goals
	Week 6 - face to face visit to debrief re the StepUp program, and counsel re future plans for physical activity
Pedometer	MP-100 pedometer (Yamasa Corp; Chiba, Japan)
Step count targets	Step count targets for each week are negotiated with the therapist during the fortnightly phone call. Where the average daily step counts is < 6000 in the preceding week, the progressive goal aims to increase daily step counts by 10% compared with the previous week. Where the average daily step counts is > 6000 in the preceding week, the progressive goal aims to increase daily step counts by 5% compared with the previous week. Note that the 6,000 step cut off was based upon our previous research with children with cerebral palsy [9,11].
StepUp handbook educational info & weekly topic	Background info on using a pedometer, dealing with fatigue/pain/injuries, and how to contact the physiotherapist.
	Week 1 – “why be physically active”
	Week 2 – “how much is enough?”
	Week 3 – “Screen time”
	Week 4 – “Staying motivated”
	Week 5 – “Myth busters”
	Week 6 – “Step it up!”
StepUp challenges	The StepUp handbook contains a number of 'mini challenges’ which participants can complete, such as “Half Hour Hero” (for taking 2000 steps in 30 minutes), “Early Bird” (1000 steps before school), “Nature Lover” (5000 steps going for a nature walk), “Shopaholic” (2000 steps at a shopping centre) etc.
Tourist circuit	Steps are tallied at the end of each week, and young people can see how far they have walked (e.g. 55,000 steps = “Mad Marathon” (approx. 42 km); 450,000 steps = “Euro Tripper” (walking approx. 343 km, the distance from London to Paris).
Wall chart	Young people are encouraged to hang the wall chart in a prominent place (e.g. the fridge or their bedroom) and mark off, or use provided stickers, to chart when they have met their daily step goal, and when they have earned “badges” for the challenges and tourist circuit.
Rewards	Participants are encouraged to negotiate rewards with their parents for meeting their daily step count target. The parent booklet gives many ideas for rewards (including rewards which have no cost).
Parent booklet	Parents receive a booklet with information for supporting their child in the StepUp program including negotiating rewards, ideas for encouraging the child and the whole family to be active, and the physiotherapist’s contact details.

**Figure 1 F1:**
[figure not shown]
**Examples of the Step Up program materials.** Upper left panel: Step Up booklet cover; Upper right: example of weekly topic (“Screen time”); lower left: example of weekly log sheet for recording daily steps; lower right: wall sticker chart, including stickers for reaching daily step goal and stickers for extra challenges.

### Control condition

Participants randomised to the control condition are being told that their health will be monitored for 20 weeks, and are placed on a waiting list and provided with the full StepUp program at completion of the study.

### Program evaluation

Participants’ experiences and views regarding the StepUp program are being evaluated using a purpose-designed feedback survey (Additional file 1). At the end of the intervention, participants in the intervention group are invited to complete a 13-item feedback form, containing a combination of Likert-scale and open-ended items regarding what they thought of the various elements of the program, and what they liked, disliked and ideas for improvement. Participants’ daily step counts throughout the 6-week program are collected by the physiotherapist during the phone call and face-to-face appointments, and will be used to determine engagement and adherence with the program.

### Analysis

A priori power analyses indicate that a sample of 42 will be required to detect a medium size within-between group interaction (f = 0.20), while a sample of 74 will be required to detect a small-medium size within-between group interaction (f = 0.15), assuming three repeated measures, two groups, an alpha-level of 0.05 and power of 80%. The change in outcomes from baseline to 8 weeks and 20 weeks, within and between groups, will be analysed using random-effects mixed-modelling, on an intention-to-treat basis. The relationship between primary and secondary outcomes and demographic variables will be assessed and where relationships exist the demographic variables will be used as covariates.

Data from the feedback survey and engagement data will be analysed descriptively. In addition, sub-group analysis will be undertaken to determine whether the intervention effectiveness is related to engagement/adherence.

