**Methods/design:**

A target sample of 70 young people with physical disabilities (aged 8–17 years, ambulant with or without aid, residing in Adelaide) will be recruited. Participants will be randomly allocated to either intervention or control following completion of baseline assessments. Assessments are repeated at 8 weeks (immediately post intervention) and 20 weeks (12 weeks post intervention). The primary outcome is objective physical activity determined from 7 day accelerometry, and the secondary outcomes are exercise intention, physical self-worth, quality of life and fatigue. Analyses will be undertaken on an intention-to-treat basis using random effects mixed modelling.

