### Outcome measures

Assessments are being conducted at three data collection time points (baseline, week 8 and week 20). The baseline assessment is conducted face-to-face at four sites located throughout metropolitan Adelaide, while the 8 week and 20 week assessments are conducted via the post. Assessments are delivered by non-blinded research personnel, however, there is minimal potential for bias given that the outcome measures are self-administered (i.e. surveys) by participants. Research personnel have been trained in the need to deliver the outcome measures in an impartial manner. Participants who complete all three assessments will receive $50 honoraria in recognition of the time and effort involved in undertaking the accelerometry and survey assessments.

At each assessment point, participants will complete the following measures:

1. Primary outcome: objective physical activity.

Objective physical activity is being assessed using Actigraph GT3X + accelerometers (ActiGraph, Pensacola, FL). The accelerometer is worn at the waist on an elasticized belt, on the right mid-axillary line. Participants are requested to use a wear-time log sheet to record time the device is put on and removed, as well as sleep and nap times. Since other studies have reported problems with meeting minimum-wear-time requirements with a waking hours protocol (i.e. daily instrument removal for sleep), participants are encouraged to wear the accelerometer 24 hours per day for 7 consecutive days. Accelerometers are initialized using ActiLife software [19], with an epoch length of 1 second and sampling rate of 80 Hz. Accelerometers are returned to the study site by reply-paid mail, at which time the research team verify the data for completeness using ActiLife software. Sixty minutes of consecutive zeros is being used to define invalid minutes (i.e. minutes in which the accelerometer was not worn). The minimal amount of accelerometer data that is considered acceptable is 4 days, including at least one weekend day, with at least 10 hours of valid wear time per day. If accelerometer data are incomplete, participants are asked to wear the accelerometer for an additional 7 days (to a maximum of 14 days) to ensure that the minimal data requirements are met. Accelerometers have been shown to accurately measure physical activity in children with physical disabilities (e.g. see [20,21]).

2. Secondary outcomes:

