### Randomisation

Random allocation to the intervention or control condition will take place after participants have completed all aspects of their baseline assessment.

Since age is recognised to impact children’s activity levels [29], and impairment level is associated with activity level in children with physical disabilities [9], a stratified randomised allocation procedure is being used to ensure an even balance of age and impairment levels between groups. Given the recognised effect of season on physical activity [30], blocking is being employed to ensure a close balance of participants in the intervention and control conditions throughout the study period, as recommended by CONSORT [31].

Randomisation is being achieved using four sets of opaque envelopes (Set 1: ages 8–12 years, Gillette level 7 or 8; Set 2: ages 13–17 years, Gillette level 7 or 8; Set 3: ages 8–12 years, Gillette level 9 or 10; Set 4: ages 13–17 years, Gillette level 9 or 10). Each set includes six envelopes, with three containing control allocation, and three containing intervention allocation. Randomisation is being undertaken by CM, who is provided with the participants’ ID number, age, and Gillette level, and who has no direct contact with participants.

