## Discussion

Physical activity is important for physical and psychological health, as well as for maintenance of physical function and independence in young people with physical disabilities. Despite this, there have been few rigorous studies aimed at intervening on physical activity in this population.

This project will evaluate the effectiveness of a novel pedometer-based physical activity self-management program for young people with physical disability.

Strengths and weaknesses of the StepUp study warrant discussion. The StepUp intervention has been carefully designed by a team of researchers and clinicians, which includes researchers with expertise in physical activity measurement, physical activity intervention, childhood physical disability, the development of written materials for children with learning difficulties, as well as highly experienced clinicians (physiotherapists and a psychologist). The program has been specifically designed to be low-cost and low-touch in nature, so that if it is found to be effective, it can be readily incorporated into ongoing clinical services. A strength of the study is that it involves a rigorous randomised controlled trial design, incorporating high quality outcome measures, including objective measurement of physical activity. The StepUp study is a single-site study. For budgetary and feasibility reasons, the study can only sample from a finite population (young people with physical disabilities meeting the eligibility criteria, including residing in Adelaide). We intend to invite the entire eligible population, and anticipate 40–70 participants will join the study, with a priori power analyses suggesting a sample of this magnitude should be sufficient to detect small to moderate effects, should they be present. For budgetary reasons, the follow up is only 20 weeks from baseline (12 weeks post end of intervention). Should the results of this study be affirmative, in the future it would be beneficial if the intervention could be evaluated in a larger sample, and over a longer-term period, in a multi-centre trial.

This study forms an early attempt at developing and evaluating a feasible physical activity intervention for children with physical disabilities, and findings will inform future efforts in this field, to assist young people with disabilities to achieve the benefits of physical activity.

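### The required samples of 42 and 74 are complete-data numbers, but the Discussion sets them against the number of children who join, with no allowance for lost or rejected follow-up accelerometry

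*Protocol article*

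**What the plan says.** The Analysis section states that "a sample of 42 will be required to detect a medium size within-between group interaction (f = 0.20") and that "a sample of 74 will be required to detect a small-medium size within-between group interaction (f = 0.15"). It lists the assumptions as "assuming three repeated measures, two groups, an alpha-level of 0.05 and power of 80"%. No loss or unusable-data rate is among them. The analysis is a random-effects mixed model by intention to treat.

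Three recruitment figures appear. The abstract has "A target sample of 70 young people with physical disabilities", Study sample aims for 50–70, and the Discussion says the authors "anticipate 40–70 participants will join the study, with a priori power analyses suggesting a sample of this magnitude should be sufficient" for small to moderate effects.

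Outcome measures describes how the primary outcome can go missing. The baseline visit is face to face, "while the 8 week and 20 week assessments are conducted via the post". A record must also pass a validity rule: "The minimal amount of accelerometer data that is considered acceptable is 4 days, including at least one weekend day", with at least 10 valid hours per day. Against loss, the plan has 24-hour wear, reply-paid return, a second week of wear (14 days at most) and a $50 honorarium for completing all three assessments.

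**The concern.** A calculation that assumes three measurements per child gives a number of children with usable data. The Discussion compares it with the number who join. The two agree only if nothing is lost after baseline. The primary outcome can be lost in two ways: the postal device does not come back, or the record still fails the wear rule after the second week.

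This is the only quantitative statement of what the trial can detect. If it is read as describing enrolled children, a null result will look like firmer evidence against the program than it is. The point concerns a conclusion that the article draws from its own calculation, so it is not a detail left to an unseen analysis plan.

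**Working it through.** **Inputs.** From Analysis: two groups, m = 3 measures, alpha 0.05, f = 0.20 and 0.15. From Randomisation: equal allocation ("Each set includes six envelopes, with three containing control allocation, and three containing intervention allocation"). Inferred, because together they return both stated totals: within-child correlation ρ = 0.5 and sphericity. Assumed, because the documents give none: the loss rates.

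**Step 1: reproduce 42 and 74.** For the within-between interaction F test, λ = f²·N·m/(1 − ρ) = 6f²N, with 2 and 2(N − 2) degrees of freedom.

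- f = 0.20, N = 42: λ = 6 × 0.04 × 42 = 10.08, df 2 and 80, power 80.3%. N = 40 gives 78.2%.
- f = 0.15, N = 74: λ = 6 × 0.0225 × 74 = 9.99, df 2 and 144, power 80.6%. N = 72 gives 79.5%.

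Both are the smallest equal-group totals that reach 80%. They contain no slack.

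**Step 2: power at the stated recruitment figures.** The complete-case columns use N(1 − d) children, where d is the loss. The last column is a likelihood-based mixed model (compound symmetry, ρ = 0.5) with baseline always observed: 80% of children have all three visits, 10% have baseline and week 8, and 10% have baseline only. Its range covers three effect shapes scaled to the same f: sustained, rising to week 20, and half lost by week 20.

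| Enrolled | f | No loss | 10% complete-case | 20% complete-case | Mixed model, 10% by week 8 and 20% by week 20 |
|---|---|---|---|---|---|
| 40 | 0.20 | 78.2% | 73.3% | 67.5% | 70.7–74.3% |
| 50 | 0.20 | 87.3% | 83.2% | 78.2% | 81.0–84.1% |
| 70 | 0.20 | 96.1% | 94.0% | 91.0% | 92.8–94.6% |
| 70 | 0.15 | 78.2% | 73.4% | 67.8% | 70.9–74.5% |

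At 30% complete-case loss, 70 enrolled still gives 86.5% for f = 0.20.

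**Step 3: how much loss f = 0.20 can absorb.** Solve N(1 − d) = 42. For 50 enrolled, d = 1 − 42/50 = 16%. For 70 enrolled, d = 1 − 42/70 = 40%. For 40 enrolled there is no margin.

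**Step 4: effect detectable at 80% power, complete cases.**

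| Enrolled | No loss | 10% loss | 20% loss |
|---|---|---|---|
| 70 | 0.153 | 0.162 (63 children) | 0.172 (56) |
| 50 | 0.182 | 0.192 (45) | 0.204 (40) |
| 40 | 0.204 | 0.216 (36) | 0.230 (32) |

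**Step 5: sensitivity to the inferred correlation.** The totals become 50 and 88 at ρ = 0.4, and 34 and 60 at ρ = 0.6.

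**The case against.** The strongest reply is that nothing is miscalculated. Both totals reproduce, and the Analysis section calls neither of them an enrolment number. Under the stated aim of 50–70, f = 0.20 has real room for loss. The mixed model also keeps children with partial data. The Discussion claims sensitivity to small to moderate effects without attaching 80% to it, and 70 enrolled with 20% complete-case loss still detects f = 0.172, which lies between the plan's two benchmarks. Finally, the loss rates are assumptions, and a change of 0.1 in the correlation moves the totals about as much as the loss does.

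Most of this stands, and it rules out three stronger readings that a reader might infer.

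- That 42 and 74 are arithmetic errors. They are correct for complete data.
- That the trial falls below 80% power as soon as any follow-up is lost. For f = 0.20 this is untrue at 50 enrolled up to and including 16% complete-case loss, and at 70 up to 40%.
- That attrition explains the shortfall for f = 0.15. The 74 exceeds every stated recruitment figure, so power is short before any loss. The same holds for f = 0.20 at 40 enrolled.

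What does not fall away is the comparison itself. The Discussion sets joiners against a complete-data requirement, and does so over a range that starts at 40, where there is no margin. The plan does not present the room at 50–70 as an attrition allowance. The steps against loss lower the rate, but do not justify treating it as zero.

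**Conclusion.** The point holds in a limited form. The stated totals contain no allowance for loss, and the Discussion applies them to children who join.

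The consequence depends on where recruitment ends. For f = 0.20 it is small at 50 and negligible at 70. At 40, the assumed mixed-model loss takes off a further 4 to 7 percentage points (78.2% to 70.7–74.3%). For f = 0.15 at the target of 70, it takes off about the same (78.2% to 70.9–74.5%). In both cases loss deepens a gap rather than creating it.

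The powers rest on ρ = 0.5 and sphericity, which are inferred, and on loss rates that are mine. The design is not invalidated. What is overstated is the effect the trial can be said to detect.

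**What to change.** Change the wording only, with no more children enrolled.

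- In Analysis, say that 42 and 74 are numbers with complete valid data at all three times, and give the correlation and sphericity assumed.
- State an assumed loss for the primary outcome that counts both non-return and records failing the wear rule, for example 20% by week 20.
- In Analysis and Discussion, report the effect detectable at 80% power for the analysable number expected, using the Step 4 values for 70, 50 and 40 enrolled. Add that the mixed model recovers part of the difference.
- In the Discussion, compare that analysable number, rather than the number who join, with the power figures.

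The cost is a few sentences and a slightly less favourable detectable effect. Recruitment, procedures and analysis stay as they are.

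### Read conventionally, the planned change-from-baseline comparison is valid but less precise than one adjusted for the baseline value, which is already collected on every child before randomisation

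*Protocol article*

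**What the plan says.** The Analysis section of the protocol article gives the quantity to be analysed as "The change in outcomes from baseline to 8 weeks and 20 weeks", within and between groups, using a random-effects mixed model by intention to treat.

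The same section states that "a sample of 42 will be required to detect a medium size within-between group interaction (f = 0.20") and that "a sample of 74 will be required to detect a small-medium size within-between group interaction (f = 0.15"). Both figures rest on three measurements per child, two arms, a 5% significance level and 80% power. Under Outcome measures, "Assessments are being conducted at three data collection time points (baseline, week 8 and week 20"). With only three assessments, baseline must be one of the three measures in the power calculation.

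The covariate rule in the Analysis section covers demographic variables, and only those found to be related to the outcomes. The baseline value of the outcome is not mentioned, and neither is a common baseline mean for the two arms.

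The Randomisation section says: "Random allocation to the intervention or control condition will take place after participants have completed all aspects of their baseline assessment". The baseline value is therefore unaffected by treatment and available for every randomised child.

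**The concern.** The usual group-by-time model with three responses has a separate mean for each arm at each visit, including baseline. The treatment contrast at week 8 or week 20 is then the between-arm difference at that visit minus the whole of the between-arm difference at baseline. Because allocation follows the baseline assessment, that baseline difference is chance alone. Subtracting all of it, rather than the part that the correlation between visits justifies, adds noise to the treatment effect.

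The demographic covariates do not recover this loss. With complete data, a covariate entered as a main effect moves all of a child's responses together and cancels out of the change.

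What is at stake is precision, in a trial with little to spare. The Discussion describes a finite eligible population, all of whom will be invited, and expects 40–70 to join. The Abstract's target of 70 is already below the 74 that the Analysis section gives for the smaller effect.

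**Working it through.** **Inputs from the article.** Alpha 0.05, power 80%, two groups and three measures; f = 0.20 with N = 42 and f = 0.15 with N = 74 (Analysis). 1:1 allocation, three envelopes of each kind per set of six (Randomisation). Expected N of 40–70 (Discussion).

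**Assumptions.** Rho is not stated, so a range is shown. Variance is taken as equal across visits, with the same correlation between any two visits.

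**Step 1: reproduce the stated sample sizes.** For a repeated-measures group-by-time interaction, lambda = f² × N × m / (1 − rho), with m = 3 measures, df1 = 2 and df2 = 2(N − 2). With rho = 0.5:

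- f = 0.20, N = 42: lambda = 0.04 × 42 × 3 / 0.5 = 10.08 on 2 and 80 df, power 0.803 (N = 40 gives 0.782).
- f = 0.15, N = 74: lambda = 0.0225 × 74 × 3 / 0.5 = 9.99 on 2 and 144 df, power 0.806 (N = 72 gives 0.795).

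Both stated figures are reproduced. A rho of 0.4 would need 50 and 88, and a rho of 0.6 would need 34 and 60. The planning calculation is therefore an ordinary interaction test with baseline among the responses and rho of about 0.5. On the same basis, power for f = 0.15 is 0.78 at N = 70 and 0.62 at N = 50.

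**Step 2: compare the two contrasts at a single follow-up.** Per child, in units of the outcome variance:

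- change score: 2(1 − rho)
- baseline-adjusted: 1 − rho²
- ratio: (1 − rho²) / [2(1 − rho)] = (1 + rho)/2

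| Assumed rho | Change score | Adjusted | Ratio | Variance reduction |
|---|---|---|---|---|
| 0.3 | 1.40 | 0.91 | 0.65 | 35% |
| 0.5 | 1.00 | 0.75 | 0.75 | 25% |
| 0.7 | 0.60 | 0.51 | 0.85 | 15% |
| 0.8 | 0.40 | 0.36 | 0.90 | 10% |
| 0.9 | 0.20 | 0.19 | 0.95 | 5% |

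**Step 3: locate the source of the loss.** Generalised least squares on all three responses at rho = 0.5 gives a variance factor of 1.00 for the week-8 and week-20 contrasts when the baseline arm difference is free, and 0.75 when the arm means are constrained equal at baseline. At rho = 0.8 the factors are 0.40 and 0.36. These match the table. The loss comes from the free baseline arm difference; keeping baseline as a response does no harm in itself.

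**Step 4: express the gain as power.** The test is taken as two-sided at 5% on one visit's contrast, with one degree of freedom and a small-sample penalty charged for the covariate. A difference with 80% power on change scores then has about 89% power after adjustment at rho = 0.5, 85% at 0.7 and 83% at 0.8, for N from 40 to 74.

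The detectable difference at rho = 0.5 falls from 0.679 to 0.588 SD at N = 70 (0.593 with the penalty), and from 0.809 to 0.700 SD at N = 50 (0.708 with the penalty). At rho = 0.8 and N = 70 it falls only from 0.430 to 0.430 × √0.90 = 0.408 SD.

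**The case against.** The strongest objection is that the article never writes out the model. It gives no list of fixed effects and does not say how baseline is parameterised. A mixed model with a common baseline mean also estimates change from baseline within and between groups, so it would fit the wording. Reproducing 42 and 74 shows which formula was used for planning, not how the final model treats the baseline arm difference. A fuller plan could already contain the adjustment. This stands, and it makes the point conditional on the conventional reading. That reading remains the natural one, because the stated target, the interaction used for power and the covariate rule all point to it.

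Second, the correlation is unknown. The value 0.5 is solved back from the sample sizes and says nothing about 7-day accelerometry in these children. Ages 8–17 and Gillette levels 7–10 imply stable differences between children, so a higher correlation, and hence a smaller gain, is plausible. This also stands. A reader might infer that the trial loses the equivalent of a third of its sample, 70 children doing the work of 70/0.75 = 93. That holds only at rho = 0.5 and should not be taken as the size of the problem.

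Third, allocation is stratified by age and Gillette level, both chosen for their link with activity. This limits chance imbalance in baseline activity but does not remove it.

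**Conclusion.** The point holds as a loss of efficiency under the conventional reading of the Analysis section. The single-visit contrast has (1+rho)/2 of its variance after adjustment: a reduction of 25% at the correlation that reproduces the plan's own sample sizes, and between 35% and 5% as rho runs from 0.3 to 0.9. This rests on equal variances and a common correlation across visits, and on a baseline arm difference left free, which the article implies but does not state.

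Two stronger inferences are not supported. A reader might conclude that chance baseline imbalance biases the result through regression to the mean. Under randomisation the change-score contrast is unbiased; imbalance affects the single estimate obtained, which is what the larger variance already expresses. A reader might also conclude that baseline should not be among the responses. Step 3 shows that three responses with equal baseline means are as precise as covariate adjustment.

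The stated sample sizes are correct for the design they assume, and the power calculation agrees with the stated analysis. The change is worth making because the expected recruitment leaves little margin and adjustment costs almost nothing.

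**What to change.** In the Analysis section, or in the full analysis plan, specify one of two equivalent models:

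- a mixed model of the week-8 and week-20 outcomes with the baseline value of that outcome as a covariate, allowing a baseline-by-time term; or
- a mixed model of all three responses with the arm means constrained equal at baseline.

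In either case, report the adjusted between-arm difference with its confidence interval at week 8 and at week 20. If a fuller plan already does this, one sentence saying so is enough.

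The cost is a change of wording and about one degree of freedom, negligible at 40–70 children. It needs no further recruitment, visits or data.

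### Covariates are chosen by their observed relation to each outcome, with no stated criterion, while the stratification factors (age band, Gillette band) are not fixed in the model

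*Protocol article*

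**What the plan says.** **Covariates.** The Analysis section gives one rule in two steps. First, "The relationship between primary and secondary outcomes and demographic variables will be assessed". Then, "where relationships exist the demographic variables will be used as covariates". It does not list the candidates, say what counts as a relationship, or say whether one covariate set serves all outcomes. The rule covers one primary and four secondary outcomes, so five models.

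**Model.** Change from baseline to 8 and 20 weeks "will be analysed using random-effects mixed-modelling, on an intention-to-treat basis". No stratum term is named.

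**Randomisation.** The Randomisation section says that "a stratified randomised allocation procedure is being used to ensure an even balance of age and impairment levels between groups". The first two envelope sets are "Set 1: ages 8–12 years, Gillette level 7 or 8; Set 2: ages 13–17 years, Gillette level 7 or 8"; the other two repeat the age bands for Gillette 9 or 10. The reasons given are that age affects children's activity and that "impairment level is associated with activity level in children with physical disabilities".

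**The concern.** The two sections do not fit together. The design treats age and impairment as known correlates of activity, the domain of the primary outcome. The analysis then treats covariate relations as something to be found in the data. Age is a demographic variable, so it can enter, but only if it passes an undefined screen. Gillette level is a functional grade, and on a narrow reading of demographic it would never be a candidate.

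Two things are at stake. One is stability: which terms are in the model, and whether they are the same for all five outcomes, depends on chance associations and on an analyst who has been given no criterion. The other is precision: stratified allocation balances the arms on the strata, and an analysis that leaves prognostic strata out keeps their variance in the standard error. The test is then conservative.

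**Working it through.** **1. The plan's own figures, and the test they describe.** The stated sample sizes are for a group-by-time interaction with 2 groups, 3 measures, alpha 0.05 and power 80%. Use λ = f²·N·m/(1−ρ), df1 = (k−1)(m−1), df2 = (N−k)(m−1), with k = 2 and m = 3. The correlation ρ is not stated; 0.5 is assumed.
- f = 0.20, N = 42: λ = 0.04·42·3/0.5 = 10.08, df 2 and 80, power 0.803.
- f = 0.15, N = 74: λ = 0.0225·74·3/0.5 = 9.99, df 2 and 144, power 0.806.

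Both figures reproduce, and this point does not alter them. They show that the powered test is a contrast of change over time, which matters in step 4.

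**2. Stability of the screen.** A threshold of p < 0.05 is assumed, since none is given.
- Simulation with N = 70, four strata, blocks of six, one follow-up value, and the two stratum factors sharing R² equally: a truly prognostic factor was selected in about 47%, 77% and 93% of trials at R² = 0.1, 0.2 and 0.3.
- A covariate unrelated to all five outcomes is picked for at least one with probability 1 − 0.95⁵ = 0.23, if the outcomes are independent.
- If each outcome had a 50% chance of selecting a given covariate, all five would agree with probability 0.5⁵ + 0.5⁵ = 0.06.

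**3. Precision if the strata predict the analysed quantity.** Let R² be the share of that quantity's variance explained by the strata (assumed; not in the article). With perfect balance, the true size of a nominal 5% test that omits them is 2·(1 − Φ(1.96/√(1−R²))), and the equivalent sample-size multiplier is 1/(1−R²). The simulation of step 2 (4,000 null runs; 2,000 runs at an assumed standardised difference of 0.68) gives the other columns.

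| R² | Size omitted, formula | Size omitted, simulated | Size fixed | Size screened | Multiplier | Power omitted / screened / fixed |
|---|---|---|---|---|---|---|
| 0.1 | 3.9% | 4.1% | 5.2% | 4.8% | 1.11 | 0.82 / 0.83 / 0.84 |
| 0.2 | 2.8% | 3.6% | 5.5% | 5.6% | 1.25 | 0.83 / 0.88 / 0.89 |
| 0.3 | 1.9% | 2.0% | 4.2% | 4.2% | 1.43 | 0.84 / 0.92 / 0.92 |

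The screened columns take both strata as candidates. On that reading, most of the power gain is recovered and size stays near nominal (4.8% also at R² = 0.4).

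**4. The planned contrast.** Age band and Gillette band do not change over the trial, so an effect on the level of activity cancels from change. This was checked in one simulated mixed-model dataset with N = 70 and strata affecting level only:
- Complete data, no strata: interaction estimates 0.0538 and −0.325, SE 0.2174.
- Strata added as main effects: identical.
- Strata crossed with time: 0.0532 and −0.3216, SE 0.2201.

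In a second dataset with 20% of follow-up visits missing, the estimates were 0.2937 and 0.4996 without strata, 0.3046 and 0.4904 with main effects, and 0.3533 and 0.4863 with strata crossed with time. These are single datasets: they show that the terms then matter, not by how much.

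A further simulation of 20,000 runs (N = 40 and 70, R² 0.1 to 0.3, level effects only) gave a size of 4.8–5.2% for a change-score test without strata, the same as with them. The fall to about 4.1% down to 2.1% appeared only for a follow-up value analysed without baseline.

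**The case against.** The strongest reply is that the planned test is a change contrast and the article links the strata only to the level of activity. With complete data, stratum main effects then do nothing to the group-by-time estimates, whether they are screened in, fixed or omitted. This stands. It means that the figures in step 3 cannot be read as this trial's expected loss. They apply only if the strata explain that share of the variance of change, or of follow-up given baseline, and the article does not show this.

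It is also fair that the rule would often admit a strongly prognostic factor, and that a condensed article may leave the full list of model terms to an analysis plan. But the article is not merely silent here. It states a selection rule, and that rule conflicts with its own reason for stratifying.

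A reader might infer that the screen inflates false positives. The simulation does not support this: mechanical selection on the outcome held type I error at 0.042 to 0.056, and omitting strata errs on the conservative side. A reader might also infer that covariates will be chosen after unblinding. The article gives no timing, and the screen relates outcomes to demographic variables, not to arm. What remains is discretion without a stated criterion, and its effect cannot be quantified from the article.

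**Conclusion.** The point holds at moderate severity. The stated rule allows different models for five outcomes with no criterion, and the two factors that the design itself singles out are not secured in any of them. The likely harm is an unstable model and some lost precision with a conservative test. False positive findings are not shown.

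The size of the precision loss is unknown. It is near zero for complete-data change contrasts if the strata affect only the level of activity. It grows if they predict change, or follow-up given baseline. The claim that leaving out the strata always widens the standard errors, or that fixing them is worth 11–43% more children here, goes beyond the article. All R² values, the p < 0.05 threshold, the difference of 0.68 and the independence of outcomes are assumptions.

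Complete data should not be taken for granted: both follow-up assessments are done by post, and accelerometer records must meet a minimum wear rule. The stated sample sizes are unaffected.

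**What to change.** Replace the screening sentence with one model for every outcome: arm, time, arm by time, age band (8–12/13–17) and Gillette band (7–8/9–10), with each stratum factor also crossed with time so that it can act on the change contrasts. Handle baseline once: either as one of the three repeated responses or as a covariate for the 8- and 20-week values, not both. Report any other demographic adjustment as a labelled sensitivity analysis.

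The cost is small. Both factors are already supplied for randomisation, so no new data are needed. With three repeated responses, the strata use 2 + 2·2 = 6 parameters; with two follow-up responses, 2 + 2·1 = 4. In a sample of 40–70 that is a few degrees of freedom. In the complete-data example, where the strata did not predict change, crossing them with time raised the standard error by 0.2201/0.2174 − 1 = 1.2%. If the plan moves baseline from response to covariate, that is a change to the stated analysis and should be recorded as one.
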